
## Results

This RCT was funded by the National Cancer Institute (1R01CA258668) in March 2022. Recruitment is planned to begin by February 2023 and will continue for 3 years.

## Discussion

### Principal Findings

This study protocol details an RCT to evaluate the psychosocial efficacy of eSCCIP/eSCCIP-SP, a novel digital health intervention for parents and caregivers of children with cancer. The development of eSCCIP and eSCCIP-SP was thoughtfully guided by the psychology, culturally competent care, and technology literature. Considering the recent and ongoing COVID-19 pandemic, the need for flexible, acceptable, and accessible psychosocial digital health intervention is more apparent than ever before to provide evidence-based psychosocial care for parents and caregivers of children with cancer. We hypothesize that the intervention will be more efficacious than an education control at decreasing negative symptoms of acute distress, anxiety, and PTSS symptoms while demonstrating improvements to coping self-efficacy and positive cognitive coping strategies.

### Comparison With Prior Work

Despite the well-documented and established psychosocial needs of parents and caregivers of children with cancer as well as challenges to in-person engagement, exceedingly few digital health options have been evaluated to provide care to this population. To our knowledge, the web-based adaptation of the Bright IDEAS Maternal Problem-Solving Skills Training Intervention [16,33,34] is the only existent psychosocial digital health intervention for parents and caregivers of children with cancer. This intervention provides education to improve problem-solving skills.

The proposed study is innovative for several key reasons. The availability of an evidence-based, psychosocial digital health intervention for parents and caregivers of children with cancer available in English and Spanish is novel, especially given its hybrid format of including both self-guided web-based content and live telehealth sessions with a trained interventionist. This format capitalizes on recommendations from prior electronic adaptations of manualized psychosocial support for parents and caregivers of children with cancer, which has suggested that web-based content may be most effective when combined with in-person contact and support [33]. The eSCCIP/eSCCIP-SP intervention has been rigorously designed and developed and is now ready for large-scale testing. Second, the development of eSCCIP/eSCCIP-SP used a systematic participatory process with multiple groups of stakeholders at all stages of design and initial testing, increasing the likelihood that the intervention is responsive to participant needs and reflects the “true” needs of the target population. In addition to working closely with parents and caregivers of children with cancer, we also partnered with trained medical interpreters and experts in cultural intervention adaptation when developing the eSCCIP-SP. Although this type of participatory research is increasingly important and well used in social and behavioral research, it is not yet commonplace in pediatric psychosocial oncology and further serves to distinguish our tools and approach. Third, the eSCCIP-SP is innovative, given the lack of resources available to the high-risk population of parents and caregivers of children with cancer, who are of Latinx descent, and the potential of the intervention to reduce systemic health care disparities related to psychosocial services. Fourth, eSCCIP/eSCCIP-SP can be used anywhere with an internet connection (including cellular telephone data access or Wi-Fi) and is adaptable/responsive to devices (eg, mobile phones), decreasing barriers to access and making the intervention highly amenable to eventual broad and rapid dissemination. While delivering web-based psychosocial interventions itself is not altogether novel, these interventions are largely unavailable for parents and caregivers of children with cancer. This is especially timely given the recent rise and acceptability of telehealth and video platforms for health care service delivery during the COVID-19 pandemic. Fifth, we will use an advanced platform to closely track engagement metrics, which will allow us to develop and quickly implement stepped care plans for future implementation studies. This platform has been developed by the Center for Behavioral Health and Technology at the University of Virginia and is used successfully to manage numerous behavioral and psychosocial digital health intervention trials, including large studies in adult oncology and adolescent oncology [60-62].

### Limitations

It is possible that the sample of parents and caregivers of children with cancer who opt to participate in our research are self-selected and may not fully represent the population of caregiving individuals of children with cancer. To identify and more broadly implement successful recruitment, retention, and engagement strategies, the primary study team recently published a manuscript describing qualitative data from focus groups and interviews [36]. The sample included past eSCCIP participants and parents and caregivers of children with cancer who were naïve to eSCCIP (but viewed some intervention content prior to participating). By implementing these strategies broadly over the course of the study, a wide range of potentially eligible parents and caregivers of children with cancer will be targeted for inclusion. We will monitor recruitment and enrollment rates closely over the course of the study, adjusting recruitment strategies if indicated. It is also possible, given both the duration of the study follow-up and randomization procedures, that participants may drop out or be lost to follow-up. Efforts by research staff to maintain participation in the study and to obtain postintervention measures for all participants will be made, including participants providing multiple means of contact to aid in follow-up as well as receiving study payments after completion of each data collection time point. In eSCCIP development trials, close tracking and monitoring procedures led to high retention rates for participants who begin the intervention, and the addition of automated reminders and a stepped care approach to communicate with participants will bolster these efforts. The characteristics of completers versus noncompleters will also be examined for systematic differences, and we will use an intent-to-treat design for data analyses.

Second, since the intervention involves an active intervention component, including telehealth follow-up with a trained guide for participants allocated to eSCCIP/eSCCIP-SP, blinding of guides is not possible. However, study team members not involved in intervention delivery will not have access to random assignment information. After randomization, participants will be instructed on the procedures within their assigned group. All outcome measures will be completed directly on the internet by study participants, further reducing the risk of bias.

Finally, it is also important to acknowledge that care at study sites includes access to psychosocial support; however, the use of these services is likely to be equivalent across intervention and control group participants, and no participant in either condition will be discouraged from accessing any available psychosocial support. While usual care may include work with a licensed psychologist, novel aspects of eSCCIP are unique to the intervention and not a component of routine care. We will also collect information on mental and psychosocial health services used by all participants during the study period to understand the context in which eSCCIP/eSCCIP-SP was received and control for other psychosocial services in analyses if indicated.

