**Methods:**

Using a randomized controlled clinical trial design, 350 eligible parents and caregivers of children with cancer will be randomly assigned to the intervention (eSCCIP/eSCCIP-SP) or an education control condition. Data will be collected at 3 time points: preintervention (prior to randomization), immediately post intervention (after 6 weeks), and at a 3-month follow-up (from baseline). Participants randomized to either condition will receive study material (eSCCIP/eSCCIP-SP intervention or education control website) in English or Spanish, based on the primary language spoken in the home and participant preference.

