### Study Outcomes

Data will be collected at 3 time points: prior to beginning the intervention (T1), postintervention (after 6 weeks; T2), and at 3-month follow-up (3 months after baseline; T3). Outcome measures include the Psychosocial Assessment Tool (PAT) [39,40], the Multidimensional Scale of Perceived Social Support [41], the Kessler Psychological Distress Scale (K-6) [42,43], the COVID-19 Exposure and Family Impact Scale [44], the Coping Self-Efficacy Scale [45], the Cognitive Emotion Regulation Questionnaire [46], Distress Thermometer [47], the Patient-Reported Outcomes Measurement Information System Short Form (PROMIS Short Form v1.0—Anxiety-8a) [48], the posttraumatic stress disorder checklist [49], as data on previous psychosocial service usage. Individuals randomly assigned to the intervention condition will also complete a questionnaire at T3 measuring satisfaction and acceptability with the intervention, which has been used in all prior eSCCIP studies. Measure description and schedule for data acquisition are provided in Table 1.

**Table 1 table1:** Outcome measures and assessment timing schedule.

Domain or measure	Description	T1^a^	T2^b^	T3^c^
Chart review	Review of patient medical record			
Demographic variables of parents and caregivers of children with cancer	Demographic variables of enrolled parents and caregivers of children with cancer	✓		
Previous psychosocial service usage	Questionnaire to measure contact and work with social work, psychology, psychiatry, pastoral care, community, and hospital-based services for all members of the family	✓	✓	✓
PAT^d^	Brief parent report screener of psychosocial risk [39,40]	✓		
MSPSS^e^	Questionnaire to measure perceived social support from family, friends, and significant other [41]	✓	✓	✓
K-6^f^	Questionnaire to measure acute distress [42,43]	✓	✓	✓
CEFIS^g^	Questionnaire to measure the extent to which a family has experienced or been “exposed” to COVID-19–related potentially traumatic events (eg, economic changes, illness in family) and the impact of these events on the family’s functioning and well-being [44]	✓	✓	✓
CSES^h^	Questionnaire to measure the perceived ability to cope effectively with challenging situations across 3 domains (use problem-focused coping, stop unpleasant emotions and thoughts, and get support from friends and family) [45]	✓	✓	✓

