The incremental (ie, beyond the cost of an education control website) costs and cost-savings analysis will follow best practices. We will estimate incremental costs associated with eSCCIP/eSCCIP-SP treatment, costs per participant, and marginal costs per unit of acute distress reduction. All costs will be estimated and evaluated in constant dollars using the appropriate index for price adjustment. Those resources that rise at the rate of general inflation will be corrected for inflation with the consumer price index, while medical costs will be adjusted with the medical component of the consumer price index. Due to the efficacy trial nature of this project, we will conduct a partial economic evaluation to document the cost information of the eSCCIP/eSCCIP-SP and estimate a preliminary cost-effectiveness regarding the primary outcome (ie, acute distress reduction). We will evaluate the intervention costs from health care provider perspective; therefore, the nonresearch-related cost/resource will be those health care provider–related ones, which will include intervention labor costs for hourly wages including fringe benefits of delivery staff for a different component of the program (ie, website regular maintenance staff, and telehealth guide). During all phases of development and implementation, we will document what was performed, by whom, the length of execution, and the use of any nonhuman resources. Cost collection instruments will be modified based on the eSCCIP guide/research team templates and behavioral intervention templates. Care will be taken to accurately separate research-based costs (eg, costs of follow-up assessments) from actual worksite program implementation costs. We will estimate separate costs for eSCCIP and eSCCIP-SP to provide the information needed to compare differences and provide evidence for predicting costs based on patients’ ethnicity distribution. To capture cost savings from a health care provider’s perspective, we will use electronic patient record to track control group patients’ related health care service usage, which provides the relevant information to estimate potential cost savings patients in the treatment group could have used if there is no eSCCIP/eSCCIP-SP. A full-scale cost-effectiveness analysis will be out of the scope of this efficacy study. We will calculate incremental cost-effectiveness ratios and will use bootstrapping methods to account for the uncertainty around the incremental cost-effectiveness ratios but recognize that the limited scope of this study: only collecting partial information on program costs, especially on implementation costs [59]. We will calculate net benefits, benefit-cost ratio, and return on investment (return on investment=net benefits/costs×100). Bootstrapping will be used for CIs construction around those measures. Generalized linear models will be applied to estimate the relationship between program incremental costs and the characteristics of participants, providers, and programs. Appropriate link function and distribution family will be chosen to fit the data. A 2-part model will be used to examine and handle sample selection and nonrandom attrition.

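### The Limitations section leaves open adjusting efficacy analyses for psychosocial services used after randomization; if that were done, the estimate would no longer be the intent-to-treat effect

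*Protocol article*

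**What the plan says.** All references are to the protocol article.

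- **Limitations, what is collected:** "We will also collect information on mental and psychosocial health services used by all participants during the study period". The same sentence gives two purposes: to describe the setting in which the intervention was received, and to "control for other psychosocial services in analyses if indicated". It names no endpoint, model, trigger or time window.
- **Limitations, what is expected:** the section asserts, without data, that "the use of these services is likely to be equivalent across intervention and control group participants". It leaves access to other support unrestricted in both arms. The same section promises an intent-to-treat design.
- **Study Outcomes, Table 1:** the instrument is described as "Questionnaire to measure contact and work with social work, psychology, psychiatry, pastoral care, community, and hospital-based services for all members of the family", with check marks at T1, T2 and T3. The Methods part of the abstract places T1 before randomization.
- **Aim 1: Analyses:** the primary model is an ANCOVA on the K-6 with the preintervention score as covariate. Further covariates enter when baseline differences are found in site, delivery or demographic variables. Service use is not named.
- **Aim 3: Analyses:** health care use in the control group will be tracked through the electronic record "to estimate potential cost savings patients in the treatment group could have used if there is no eSCCIP/eSCCIP-SP".

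**The concern.** One sentence joins the collection of services used during the study to the intention to control for them, so on its plain reading the covariate is measured after randomization. Parents in more distress may seek more help, and an effective intervention may alter help-seeking. On-study use can therefore be a consequence of both allocation and distress. Conditioning on such a variable can remove part of the effect, exaggerate it, or bring in an association that randomization had excluded.

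The condition in the sentence gives little protection. Because the text has just said that use should be equal across arms, the natural reason to adjust is an observed difference. Such a difference may be chance or an effect of allocation, and the data do not say which. If it is an effect of allocation, the adjustment can bias the result.

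At stake is the question in Specific aim 1: whether the intervention lowers distress more than the education control, with other support available as usual in both arms.

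**Working it through.** **1. The plan's own figure.** Inputs from Power Analyses and Sample Size Consideration: difference 0.3 SD, pre-post correlation 0.5, power 80%, level .05 (two-tailed, from Aim 1: Analyses), attrition 25%.

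- Residual SD = √(1 − 0.5²) = 0.866.
- n per arm = 2 × (1.960 + 0.842)² × 0.75 / 0.3² = 130.8, so 131 per arm and 262 in total.
- 262 / (1 − 0.25) = 349.3, so 350.

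The stated 350 is reproduced and is not in dispute.

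**2. What the adjustment does.** Let *a* be the effect of allocation on service use (SD units, by any route). Let *γ* be the slope of the outcome on service use, given arm and baseline distress. In a linear model,

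adjusted effect = total effect − *γ* × *a*.

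The shift is zero if *a* = 0. Its sign depends on whether use mainly marks distress (*γ* > 0) or relieves it (*γ* < 0), and on whether the intervention lowers or raises use.

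**3. Assumed values.** The protocol gives none of these, so they are assumptions. Baseline distress acts on use with coefficient 0.3, which leaves variance 1 − 0.3² = 0.91 in use.

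- *Shared driver:* interim distress acts on use (0.4) and on the outcome (0.5), so *γ* = 0.4 × 0.5 / 0.91 = 0.22.
- *Mediator:* use lowers distress, *γ* = −0.20.
- *Both:* *γ* = 0.22 − 0.20 = 0.02.

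**4. Adjusted estimate when the total effect is −0.30 SD.**

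| Arm effect on use, *a* | Shared driver | Mediator | Both |
|---|---|---|---|
| 0 | −0.30 | −0.30 | −0.30 |
| −0.1 | −0.28 | −0.32 | −0.30 |
| −0.2 | −0.26 | −0.34 | −0.30 |
| −0.3 | −0.23 | −0.36 | −0.29 |
| +0.2 | −0.34 | −0.26 | −0.30 |

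Example: shared driver, *a* = −0.3, gives −0.30 − (0.22 × −0.3) = −0.30 + 0.066 = −0.234. A simulation with 2,000,000 records per scenario agreed with the formula to within about 0.002 in these scenarios.

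**5. Power.** At 131 per arm, holding the residual SD at 0.866 (an approximation), the shared-driver estimates of −0.28, −0.26 and −0.23 correspond to power of about 0.74, 0.67 and 0.59, against 0.80 for the unadjusted effect. In the mediator case with *a* = −0.3, the figure rises to 0.92. That gain comes from an estimate that overstates the total effect.

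**The case against.** The sentence is a contingent remark in the Discussion. The section that governs the analysis, Aim 1: Analyses, does not list service use, and the article commits to intent-to-treat. The first stated purpose of the data is context, so the remark is compatible with a sensitivity analysis, and a statistical analysis plan not shown here could give it that role. Separating the intervention from concurrent psychosocial care is also a legitimate secondary question. All of this stands and limits the point. It does not remove it, because nothing in the article confines the adjustment to T1 use or to a secondary role.

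Three stronger readings are tempting, and the document does not support them.

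- *The primary analysis will be adjusted and therefore biased.* The adjustment is conditional and absent from the stated primary model, and there is no bias if allocation leaves service use unchanged.
- *Aim 3 assumes that the intervention reduces service use.* It will estimate potential savings, from the health records of control-group patients rather than from the family questionnaire. This shows that an effect is thought possible, no more.
- *Adjustment would predictably shrink the effect, for instance by a factor 1 − r², with r the within-arm correlation of use and outcome.* That formula is right only if the outcome score itself drives service use, and it leaves out the baseline score. Services used before T2 cannot be caused by the T2 score. With other orderings the estimate can grow, shrink or stay put.

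**Conclusion.** The point holds in a conditional form. The article states an intention to control for a post-randomization variable without saying in which analyses. If this were done in an efficacy model, the estimate would not be the intent-to-treat effect that the same section promises, and the covariate rule would extend beyond the baseline differences named in Aim 1: Analyses.

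The size cannot be determined from the document. It is zero when allocation does not change service use. Under the assumed path strengths it reaches about 0.07 SD in either direction against 0.30 SD, and opposing paths can nearly cancel. These figures rest on a linear model and on coefficients chosen for illustration; they show that the direction cannot be known in advance. The planned sample size is unaffected.

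**What to change.** Replace the closing clause of the sentence in Limitations, and add a matching line to Aim 1: Analyses, to say that:

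- only service use reported at T1, before randomization, may be a covariate in the primary and secondary efficacy models;
- service use at T2 and T3 will be reported and compared by arm;
- any model that includes on-study service use will be labelled exploratory or mediation and will not support the efficacy conclusion.

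This keeps room for the secondary question about concurrent care. The cost is wording only: the T1 measure is already scheduled, no data collection is added, and the sample size stays at 350.

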### Dissemination Plan

Data will be disseminated and shared with the scientific community through peer-reviewed publications and academic conference presentations. Furthermore, the results will be shared with participants through annual updates. Continual efforts to disseminate study progress and results are valued to maintain productive and collaborative relationships with institutional care teams and relevant stakeholders. A summary of study results will be submitted to ClinicalTrials.gov within 1 year of the trial’s primary completion date.

### Conclusions

Despite advances and improved medical outcomes for childhood cancer, parents and caregivers of children with cancer are at known risk for negative psychosocial sequelae, including increased risk for Latinx, Spanish-speaking parents and caregivers of children with cancer [1,2,12]. Established standards of care recommend access to high-quality psychosocial support for parents and caregivers of children with cancer and, while digital health interventions may address many logistical barriers to in-person participation in this population [63], few options exist at this time. The results from rigorous development, refinement, and pilot testing of eSCCIP and eSCCIP-SP have demonstrated the potential to deliver an effective and easily disseminatable intervention, decreasing barriers to care, and improving psychosocial outcomes. Data obtained from this RCT will be instrumental in evaluating the efficacy of the eSCCIP/eSCCIP-SP intervention as an evidence-based tool to support parents and caregivers of children with cancer across the cancer trajectory.

## Abbreviations

ANCOVA: analysis of covariance
CFIR: Consolidated Framework for Implementation Research
eSCCIP: Electronic Surviving Cancer Competently Intervention Program
eSCCIP-SP: El Programa Electronico de Intervencion para Superar Cancer Competentemente
K-6: Kessler Psychological Distress Scale
PAT: Psychosocial Assessment Tool
PROMIS: Patient-Reported Outcomes Measurement Information System
PTSS: posttraumatic stress symptom
RC: research coordinator
RCT: randomized controlled trial
